### Objectives {7}

The primary objective is to determine whether immediate protected weight-bearing and ankle range of motion post-open reduction and internal fixation of unstable ankle fractures improve functional outcomes compared to postoperative ankle immobilisation in a non-weight-bearing cast; second, to determine whether the rate of complications, such as wound infection and fixation failure, with immediate weight-bearing and ROM, is comparable to the rates with the usual postoperative protocols; and finally, to determine the cost-effectiveness of this treatment method, which can be determined by the analysis of patients’ ability to return earlier to work and the detailed cost of either intervention, including the length of hospitalisation.

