## Methods: participants, interventions and outcomes

### Study setting {9}

This pRCT will be conducted at three academic trauma units at three different urban centres in Ireland. Each centre serves a referral population of >500,000 and receives all grades of trauma from urban and rural environments on a 24-h basis. A trauma team is on call daily and includes two trainee surgeons and a consultant orthopaedic surgeon. Surgeries are performed in part or in total or supervised by consultant orthopaedic surgeons. Regional and general anaesthesia is used at the discretion of the anaesthetist. Ankle fracture surgery is conducted on both a day case or an overnight basis. Ward-based physiotherapy is provided daily to facilitate early discharges. All hospital personnel contributing to the recruitment and patient pathways in this trial will undergo training in the study’s objectives and methodology.

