### Outcomes {12}

The primary outcome measure is the functional Olerud-Molander Ankle Score (OMAS) at 6 weeks postoperatively. This score ranges from 0 to 100, with 100 representing normal ankle function [15]. Secondary outcome measures include complication rate (infection and fixation failure), the entire arc of ankle motion (plantar flexion and dorsal flection) in degrees using a goniometer; RAND 36-Item Short Form Survey scoring (SF-36), from the RAND corporation [16]; the time needed to return to work in days; and postoperative hospitalisation length in days.

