### Statistical methods

#### Statistical methods for primary and secondary outcomes {20a}

Continuous outcomes and other key variables will be described by their means and SDs, medians and IQRs, and total range. Categorical variables will be described by counts and respective proportions.

The primary outcome, OMAS score at 6 weeks, will be analysed using multiple linear regression with fixed effects for study arm and centre, from which we will report the centre-adjusted difference in mean OMAS scores between the two arms with a 95% confidence interval (CI) and exact p value. The complete set of longitudinal OMAS scores, from 2 weeks to 1 year, will be analysed with the corresponding linear mixed-effects model (with the identity link function), with fixed effects for the centre, arm, and time (dummy coded) and an interaction term between arm and time. Time-specific differences in the mean OMAS scores between arms will be calculated from the model’s results, along with 95% CIs and the exact p value from the time by arm interaction.

Longitudinally measured secondary outcomes will be similarly analysed and reported: ankle range of motion with the same linear mixed-effects model and RAND-36 scores with an ordinal mixed-effects model with a logit link function (i.e. the proportional odds model). Time to return to work (in the subset working at baseline) and length of stay will be analysed using Cox proportional hazards models, with fixed effects for centre and treatment arm. Infection (any) and fixation failure at any point during study follow-up will be similarly analysed using logistic regression.

There will be no formal adjustments for multiplicity, but we will report all estimated treatment effects alongside exact p values, allowing the reader to make whatever adjustments they prefer. Any deviations from the above plan will be fully described and justified in the final report of the trial results. All analyses and the production of tables and plots will be conducted using the R (version 3.6.3, R Project for Statistical Computing) and Stata16 software. All analyses will be conducted or supervised by the principal statistician of the HRB Clinical Research Facility Cork under their quality system and relevant standard operating procedures and following regulatory guidance (e.g. ICH E9).

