#### Methods for additional analyses (e.g. subgroup analyses) {20b}

No planned additional analysis.

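### Return to work and length of stay are compared between arms only by Cox hazard ratios; add a between-arm difference in days, which the third objective needs and which stays interpretable if return-to-work hazards are not proportional

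*Protocol article*

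**What the plan says.** Four parts of the protocol article bear on this point.

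- **Outcomes {12}** lists as secondary outcomes "the time needed to return to work in days; and postoperative hospitalisation length in days".
- **Objectives {7}** sets a third aim: "to determine the cost-effectiveness of this treatment method, which can be determined by the analysis of patients’ ability to return earlier to work", together with "the detailed cost of either intervention, including the length of hospitalisation".
- **Statistical methods {20a}** gives one between-arm analysis for the two outcomes. Time to return to work (in those working at baseline) and "length of stay will be analysed using Cox proportional hazards models, with fixed effects for centre and treatment arm". The same section also promises that "Continuous outcomes and other key variables will be described by their means and SDs, medians and IQRs, and total range".
- **Intervention description {11a}** keeps group B in a cast without weight-bearing for 6 weeks, after which that group starts physiotherapy, motion exercises and weight-bearing as tolerated. Group A may bear weight and exercise from the start.

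Study setting {9} adds: "Ankle fracture surgery is conducted on both a day case or an overnight basis". Stays of zero days are therefore possible; their share is not given.

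**The concern.** The objective and the planned estimate are on different scales. A cost comparison multiplies days in hospital and days off work by a price, so it needs a difference in mean days and its uncertainty. The planned treatment effect is a ratio of rates. For the primary outcome, OMAS at 6 weeks, the same section plans a centre-adjusted mean difference with a 95% CI; for the two outcomes on which the cost objective rests, it plans nothing comparable.

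Return to work raises a second issue. The difference in permitted loading is concentrated in the first 42 days. If that restriction delays work, the hazard ratio will be large early and move towards 1, or past it, later. The single Cox ratio is then an average whose value depends on how long patients are followed. A reader could take a 1-year ratio near 1 as no benefit although days were saved, or could turn a ratio into days without a basis.

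**Working it through.** **The plan's own figure.** The protocol gives no hazard ratio, event count or number of days for either outcome, so there is nothing to reproduce. Its sample size concerns OMAS at 6 weeks only. All rates below are assumptions.

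**Step 1. A hazard ratio does not fix days.** With exponential times and control mean m, the mean saved is m × (1 − 1/HR). For HR = 1.5 this is m/3:

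| Assumed control mean (days) | Days saved at HR 1.5 |
|---|---|
| 1 | 0.33 |
| 3 | 1 |
| 30 | 10 |
| 60 | 20 |

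**Step 2. Return to work with an early, time-limited contrast.** Assume a daily return rate r up to day 42 (6 × 7 days, Intervention description {11a}), then 0.015 in both arms. Restricted mean time to day 365 is

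(1 − e^(−42r))/r + e^(−42r) × (1 − e^(−0.015 × 323))/0.015,

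where 323 = 365 − 42 and the last fraction equals 66.14.

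- r = 0.0025 (group B): 39.87 + 0.9003 × 66.14 = 99.4 days
- r = 0.010 (group A, strong early difference): 34.30 + 0.6570 × 66.14 = 77.8 days; difference 21.7 days
- r = 0.005 (group A, mild early difference): 37.88 + 0.8106 × 66.14 = 91.5 days; difference 7.9 days

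The large-sample Cox hazard ratio (A vs B), solved numerically from the same curves with follow-up cut at three of the visit times in Follow-up, is:

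| Early rates, A vs B | To 84 days | To 182 days | To 365 days | Days saved by 365 |
|---|---|---|---|---|
| 0.010 vs 0.0025 | 1.61 | 1.36 | 1.32 | 21.7 |
| 0.005 vs 0.0025 | 1.20 | 1.12 | 1.10 | 7.9 |

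As a control, rates that are proportional throughout (0.010 vs 0.005, then 0.020 vs 0.010) give 2.00 at all three cut-offs. The drift therefore comes from non-proportionality and not from the cut-off itself.

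**Step 3. Sensitivity to what happens after day 42.** Take a constant rate in group A with median 60 days (ln 2/60 = 0.01155 per day), and one quarter of that rate in group B to day 42.

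- Group B then at the same rate as A: HR 1.80 to day 84 and 1.38 to day 365; 29.1 days saved.
- Group B then at 1.5 times the rate of A (catch-up): HR 1.35 to day 84 and 1.03 to day 365; 5.2 days saved.

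In the catch-up case a 1-year ratio of almost 1 stands beside a saving of 5 days.

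**Step 4. Length of stay.** The 6-week mechanism does not reach this outcome, which ends at discharge. Zero-day stays do not by themselves distort Cox, because it uses only the order of the times. In a simulation with 40% vs 20% day cases (assumed), the hazard ratio was 1.324 with zeros coded as 0, 0.5 or 1. It changed, to 1.03, only when zero-day stays were left out. For this outcome the gap is one of scale: a ratio is planned where the objective needs days.

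**The case against.** The other side has several good points.

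- **Days are not absent from the plan.** Means and medians are promised, and stays are normally fully observed, so mean stay by arm follows directly. This stands. What it leaves open is a centre-adjusted difference with a CI and, for return to work, a mean that allows for patients who have not returned or are lost.
- **Cox is a standard choice.** It suits censored return to work and is accepted for skewed stays. This stands, and is why the models should be kept.
- **Non-proportionality is inferred.** The protocol restricts weight-bearing, not work, and some patients may work in a cast. This stands: the assumption is doubtful, not shown to fail.
- **Costing detail may sit in a separate plan.** This stands, so the lack of an economic plan in the article is not held against it.

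A reader might go further and infer any of the following; the documents do not support them.

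- *Day cases are mishandled, or the two named packages will disagree on them.* No rule in the text drops zero-day stays, Step 4 shows the coding does not matter while they are kept, and nothing in the protocol speaks to package behaviour.
- *The statement "No planned additional analysis" forbids a days-based estimate.* It stands under a heading about subgroup-type extras and does not bar analysis of an objective already declared.
- *The third objective cannot be answered.* Days are collected for each patient and can be analysed; the text simply does not name the estimate.

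**Conclusion.** The point holds in a limited form. The only between-arm estimates planned for return to work and length of stay are hazard ratios, while the cost objective relies on quantities in days. For return to work, the design makes a constant hazard ratio doubtful. Across the four assumed scenarios the 1-year ratio runs from 1.03 to 1.38 and the time saved from 5 to 29 days. These figures depend wholly on the assumed rates; the protocol gives no return-to-work or length-of-stay distribution, so the size in this trial is unknown. Both outcomes are secondary, and the primary analysis is unaffected.

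**What to change.** Keep the Cox models and add to Statistical methods {20a}:

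1. **Return to work** (those working at baseline): the difference between arms in restricted mean time to 365 days, with 95% CI, and Kaplan-Meier curves by arm.
2. **Length of stay**: the difference in mean days adjusted for centre, with bootstrap 95% CI, and a statement that zero-day stays are included.
3. **Third objective**: base the cost comparison on these two differences, and make no cost-effectiveness claim from the hazard ratios alone.

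The cost is a few sentences, a little code and one more estimate per outcome to report. No new data are needed.

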### Trial design {8}

The study will be a prospective, pragmatic randomised controlled trial (p-RCT), unblinded with participants allocated in a 1:1 ratio to one of two parallel groups. Patients will be randomised using computerised block randomisation (twenty patients per block). The study is multicentre and will include three major orthopaedic centres in Ireland.

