### Sample size {14}

An a priori power analysis for the superiority of treatment with immediate weight-bearing and ROM will be conducted for this hypothesis. To detect a clinically significant 10-point difference in the Olerud and Molander Ankle Score (OMAS) at 6 weeks, with a standard deviation of 19 [17–20], alpha = 0.05 and β=0.20 (80% power) and two-sided test and a maximum loss of follow-up of 20% (N=145), this was rounded to 160 to support the block randomisation (20 block size), and a sample size of 80 per group is necessary.

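### Fixation failure is to be compared by ordinary logistic regression with no sparse-data method, so if one arm has no failures the promised odds ratio cannot be estimated and the default (Wald) p value is close to 1

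*Protocol article*

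**What the plan says.** The harm comparison is set out in one sentence of the protocol article, Statistical methods {20a}: "Infection (any) and fixation failure at any point during study follow-up will be similarly analysed using logistic regression". The word for 'in the same way' refers back to the preceding sentence, which specifies "Cox proportional hazards models, with fixed effects for centre and treatment arm". The model is therefore logistic regression on arm and centre, with three centres (Trial design {8}).

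The same section says that all estimated treatment effects will be reported with p values given exactly. It does not say whether the logistic p value is a Wald, likelihood-ratio, penalised or exact one, and it states no method for an arm without events. It does say that categorical variables will be described by counts and proportions, and that departures from the plan will be described and justified.

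Fixation failure is one of the two complications named in the second objective (Objectives {7}). The trial is sized on the ankle score, not on complications: "a sample size of 80 per group is necessary". The only complication rate in the document is the 20% threshold in {11b}. That is a termination threshold for wound complications and fixation failure combined, not an expected failure rate.

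**The concern.** Ordinary logistic regression has no finite solution for the arm coefficient when one arm has no events. The fitting routine stops at an arbitrary large value with a very large standard error, and the Wald p value goes to about 1 however many events the other arm has.

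A control arm without failures is plausible. The exclusion criteria remove fractures in which stable fixation is not expected, and the control arm is in a cast and non-weight-bearing for 6 weeks. A table such as 0/80 against 8/80 would be the clearest failure signal the trial could produce, yet it is the kind of table for which the named model gives no usable estimate.

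This analysis carries weight because the protocol has no data monitoring committee ({21a}) and no interim analysis ({21b}). A 10% failure rate in one arm would not by itself reach the 20% threshold in {11b}. The end-of-trial regression is the planned formal comparison of this harm.

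**Working it through.** **1. The plan's own figure.** Inputs from Sample size {14}: difference 10, SD 19, and "alpha = 0.05 and β=0.20 (80% power) and two-sided test". A two-sample t-test needs 57.6, so 58 per arm, or 116 in total. Allowing for 20% loss, 116 / 0.80 = 145, which is the stated figure, rounded up in the protocol to 160. The sample size reproduces and this point does not affect it. The sizes used below are 80 per arm and, after 20% loss, 80 × 0.80 = 64 per arm.

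**2. What the named model returns.** Arm-plus-centre logistic fits, 80 per arm, equal centre sizes assumed:

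| Failures, cast v boot | Log OR (SE) | Wald p | Likelihood-ratio p | Fisher p |
|---|---|---|---|---|
| 0 v 6 | 18.7 (4,494) | 0.997 | 0.003 | 0.028 |
| 0 v 8 | 18.0 (2,720) | 0.995 | 0.0007 | 0.0065 |
| 1 v 8 | 2.18 (1.07) | 0.042 | 0.011 | 0.034 |

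In the first two rows the log odds ratio and SE only show where the iteration stopped. A second fit of these tables stopped at about 22 with SE about 14,600 and p = 0.999. For 0 v 8, z = 18.0 / 2,720 = 0.007. In the third row the estimate is finite, so the breakdown of the arm term needs zero events in an arm, not merely few.

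**3. How often an arm of 80 or 64 has no failures.** P(0) = (1 − p)^n. The rates p are assumptions, because the protocol gives none.

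| Assumed control rate | n = 80 | n = 64 |
|---|---|---|
| 0.5% | 67% | 73% |
| 1% | 45% | 53% |
| 2% | 20% | 27% |
| 5% | 2% | 4% |

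Zero control failures is more likely than not only if p < 1 − 0.5^(1/n), that is, below 0.86% at 80 per arm or 1.08% at 64.

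**4. What a penalised fit returns.** Without the centre term, Firth's estimate amounts to adding one half to each cell. For 0/80 v 8/80 the odds ratio is (8.5 / 72.5) / (0.5 / 80.5) = 18.9, which is finite, with penalised likelihood-ratio p = 0.003. For 0/80 v 6/80, p = 0.012.

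**5. Power and type I error.** Exact enumeration of both binomials, 80 per arm, arm term only, two-sided 5%, with Wald counted as non-significant when a cell is zero:

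| Assumed rates | Wald | Firth |
|---|---|---|
| 1% v 8% | 14% | 55% |
| 1% v 10% | 27% | 73% |
| 2% v 10% | 32% | 56% |
| 5% v 15% | 51% | 57% |

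At 64 per arm, 1% v 10% gives 13% v 59%. Not all of the gap comes from zero cells: Wald is also the weaker test when the control arm has one event (1 v 7: Wald p = 0.061, Firth p = 0.032). Firth's type I error is at or below 3.5% for common rates from 0.5% to 5%. The unpenalised likelihood-ratio test has type I error of 7% to 9% at common rates of 2% to 5%.

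**The case against.** **This is analysis-plan detail.** Logistic regression is a standard model for a binary outcome, and the test statistic and a separation fallback are often left to an analysis plan, which is not shown. The protocol places the analysis under an experienced statistical unit and allows justified deviations. This has force, and if the analysis plan already holds a fallback, one line of confirmation closes the point. But {20a} does more than leave the method open: it names one and promises an estimate from it. Choosing a substitute after seeing an unblinded 0 v 8 table is what prespecification is meant to avoid.

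**No Wald test is named.** This stands. The p value near 1 belongs to the default output, and a likelihood-ratio p value from the same model would be small. That rescues the p value at the price of inflated type I error at the rates shown, and it does not rescue the odds ratio.

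**The signal would not be hidden.** Counts by arm will be reported and case report forms are checked daily, so 0/80 v 8/80 would be visible. This stands too, but counts are not the promised treatment effect and p value.

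**Readings that go too far.** A reader might infer that a true excess of failures would usually be reported as p near 1. The documents do not support that, because it needs a control rate below about 0.9% (80 per arm) to 1.1% (64 per arm) and no rate is given. Zero control failures together with at least 6 boot failures (the smallest count that Fisher's test would flag against zero) has probability 9% at 1% v 5%, 28% at 1% v 8%, 12% at 2% v 8% and 2% at 5% v 15%.

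Nor do the documents support three further inferences:

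- That few events break the model: 1 v 8 fits normally.
- That a centre without events spoils the arm effect: with 2 v 8 failures and one empty centre, the arm log odds ratio was 1.509 (SE 0.816) whether that centre was kept or dropped.
- That a separate deep-infection analysis is affected: {20a} plans only any infection.

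**Conclusion.** The point holds in conditional form. If one arm has no fixation failures, the model named in {20a} yields no finite odds ratio and a default p value near 1, whatever the count in the other arm, and no alternative is stated. How likely that is depends on a rate the protocol does not give: about 67%, 45%, 20% and 2% of trials at assumed control rates of 0.5%, 1%, 2% and 5% with 80 per arm. It may happen; the documents do not show that it usually would.

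Under the assumed rates in the working, the power lost by Wald relative to Firth runs from 6 points (57 − 51, at 5% v 15%) to 46 points (73 − 27, at 1% v 10%). These figures assume that the default Wald test would be used and ignore the centre term. The change should be made because the harm is named in the second objective and the remedy is cheap. The primary analysis and the sample size are untouched.

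**What to change.** In {20a}, replace the sentence on infection and fixation failure with wording such as: 'Infection (any) and fixation failure during follow-up will each be analysed by Firth penalised-likelihood logistic regression with terms for arm and centre, with profile penalised-likelihood confidence intervals and p values. The risk difference between arms will also be reported with a 95% score (Miettinen-Nurminen) interval.' The risk difference and its interval remain defined when an arm has no events.

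The cost is one sentence. Firth regression is available in both R and Stata, the packages the protocol names, and nothing changes in sample size, data collection or conduct. The small downside is that the odds ratio is shrunk slightly towards 1 when events are few. If an analysis plan already contains an equivalent provision, a cross-reference to it in {20a} is enough.

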#### Methods for additional analyses (e.g. subgroup analyses) {20b}

No planned additional analysis.

#### Methods in analysis to handle protocol non-adherence and any statistical methods to handle missing data {20c}

Any protocol non-adherence will be disclosed and handled accordingly. An effort will be made to prevent missing data as much as possible. Unavoidable missing data, such as withdrawals from the study or loss to follow-up data, will be analysed on an intention-to-treat basis, including sensitivity analysis. Multiple imputations using chain equations (MICE) will be used for missing data [27–29].

#### Plans to give access to the full protocol, participant level-data and statistical code {31c}

The full protocol is available at the registry website and will be published in one of the trial protocol journals.

### Oversight and monitoring

#### Composition of the coordinating centre and trial steering committee {5d}

Four authors at the coordinating centre (University Hospital Waterford) take responsibility for the scientific validity of the study protocol, assessment of study quality and conduct, as well as for the scientific quality of the final study report.

#### Composition of the data monitoring committee, its role and reporting structure {21a}

The authors understand the composition for a standard data monitoring committee (DMC) for this trial is challenging and might be impossible. The lack of funding is the main barrier. Unlike a clinical trial where a DMC and interim analysis must be formulated, this non-interventional trial, with relatively small numbers, does not investigate a pharmacological or medicinal product and does not expose patients to significant harm. Both treatment methods are already part of routine practice. As such, the trial team will closely monitor any adverse event or harm that might arise and act accordingly on a daily basis (see below).

